**Fig. 2 Fig2:**
[figure not shown]
EMPOWER-PD protocol

Every 2 weeks of intervention, one pillar of EMPOWER-PD will be addressed (self-knowledge of your body (first), developing strategies for your limitations and enhancement of your abilities (second), flexibilization and development of your abilities (third) and autonomy and empowerment of health of participants for a more proactive life (fourth)). The two first weeks are periods of familiarization with the dynamics of the exercise and with the new stimulus of self-perception (for more details see Table 1). From the third week on, several materials will be introduced according to the protocol. All participants will be entering in contact with the preferences of all in a circuit system, where each step the individual will interact with a different activity and object of preference, for example, dance, sing, paint, cooking, gardening, and others, according to group and therapist creativity. The therapist will assume the role of group guide, in front of the exercises and always generate positive feedback to each exercise instruction. The positive feedback provided will be done verbally after each task, with positive reinforcement and incentive phrases during the practice of the exercise.

Specifically, in the last 2 weeks of the protocol (seventh and eighth weeks), the fourth pillar of EMPOWER-PD (winning autonomy and power for an active life), will be composed by a booklet (Additional file 3) with circuit images and suggestions of dynamics and progressions (already done in weeks 1 to 6 of the protocol) that will be chosen by the participant based on their preferences. The booklet will be formulated by the therapist according to the information from the group collected by contact with them in all sessions, being adapted for each population that receive the EMPOWER-PD. It will be composed of multiple choice options of stretching, main part, progression, preferences, and cooling; all chosen according to the group previously at the beginning of the activity. Throughout the sessions of the last 2 weeks, the therapist will become less active in the stages of construction of the exercises, duration, and frequency of the exercise, passing such responsibility to the individuals themselves. The intervention will continue to be supervised, but the therapist will be present as a source of guidance stimuli for the group, how initially controlling the time of each part, suggesting the time to progress and others according to the necessity of the group.

The warm-ups will always count on varied exercises that stimulate the activation of the body’s own perception and the relationship between the groups. The exercises will use music, interaction with their own body and their colleagues, and their suggestions of warm-up exercises based on their own knowledge about physical activity previously practiced. A “back to calm” stage will feature breathing and meditative exercises with the goal of to perceive sensations in their body after the exercise. In addition to the feedback provided after each task, at the end of each session, a talk wheel is held about their perceptions of the session and the repercussion under their daily routine.

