Based on all information above, this study presents the EMPOWER-PD protocol, a physical therapy approach based on the individual preferences. As a new intervention protocol, it is necessary to verify it feasibility when applied to the target population. This study presents the design of the feasibility randomized controlled trial that aims to(i)Investigate the feasibility of the EMPOWER-PD protocol through adherence rate, recruitment rate, and safety.(ii)Compare the preliminary effectiveness of the EMPOWER-PD with the conventional physical therapy through qualitative analysis of motivation, empowerment of health, followed by the analysis of the dependency of professional supervision by individuals to remain active in the post follow-up period.(iii)Compare the preliminary effectiveness of the EMPOWER-PD in motor and non-motor symptoms (functional mobility, gait, fatigue, aerobic capacity/endurance) with the conventional physical therapy through quantitative analysis of estimates of 95% confident interval.

We hypothesize that the EMPOWER-PD will lead to higher adherence and safety when compared with conventional physical therapy. Concerning motivation, health empowerment and dependency of professional supervision by individuals to remain active in the post follow-up period, we hypothesize that the EMPOWER-PD will be associated with better outcomes in preliminary effectiveness than the conventional physical therapy. For the motor and non-motor symptoms, we hypothesize that the EMPOWER-PD will be associated with similar preliminary effectiveness to the conventional physical therapy.

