Third–fourth Developing strategies for limitations and improving skills	Develop own strategies to overcome limitations (internal cues, imagery, sound stimuli, body adjustments). Enhance skills through their preferences.	From sitting, get up and walk in an 8-m track (passing and skirting obstacles, passing through narrow spaces (60 cm), holding objects) to the “U” (80 cm), interact with their preference, turn around, and sit on the next chair.	Attentional focus during the task: pay attention to how you go through the challenges. Realize where you have easy and difficulty. Test with your body the ways for you to overcome the difficulty and enhance what you have easily.	The “U” will decrease (80 cm–60 cm pivot) and the height of the chair (45 cm–40 cm bench). Obstacles will grow taller and narrower; the spaces will rise to 50 cm, and they will exchange objects between them during the gait.
Fifth–sixth Flexibilizing and developing confidence	Develop confidence and new strategies during walking and mobility in conflicting situations of daily living.	From sitting, get up, and walk 8 m under the same challenges of the previous week, but under more conflicting stimuli (talk to the duo during the task, different speeds, stop abruptly, traffic signal, sing, perform their concomitant preferences the task).	Attentional focus during the task: pay attention to how your body behaves in these conflicting situations. Test the strategies you already know and realize how safe you are by doing the task. Keep challenging yourself while always prioritizing your safety.	Pivot in all the ends and the height of the chair will continue of 45 cm–40 cm bench.
Seventh–eighth Winning autonomy and power for an active life	Decrease dependence on the therapist. Develop your own therapy based on your choices.	Booklet with the image of the circuit available for the free will to choose their exercises, their intensity, participants per season, and moment of progression.	As a team, choose how you guys will set up your circuit. I will be here to help you and listen to your doubts. Remember to respect your body and safety, but always progress using your individual strategies. Have fun!	At this stage, the therapist will be co-adjuvant in therapy, always stimulating the confidence and tranquility of the group and appearing in a few moments.

Legend: *m* meters; *cm* centimeters

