#### Interventions groups

The treatment sessions will be performed in group, twice a week, for 8 weeks, completing 16 sessions followed by a 4-week follow-up period. Before and after each session, blood pressure will be measured. The exercise intensity will be monitored every 5 min by an oximeter and the modified Borg scale [37] will be applied to verify the perception of effort in both groups by two physical educators for group. However, in the CPh group, the exercise intensity will be controlled between 55% and 85% of maximum heart rate (HR_max_) [2], according to the Karvonen’s formula. Each individual value will be calculated previously the interventions and vebaly stimulated during the session by the physical educator to keep up with the recommended HR values, increasing or slow walking speed. It is important to note that the intensity of the EMPOWER-PD protocol will be self-controlled according to the self-perception of effort of each one. The activities will be carried out during the “on” phase of the medication lasting 1 h, divided into 10 min of heating, 40 min of main part, and 10 min of back to calm [38] in an outpatient space.

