**Fig. 3 Fig3:**
[figure not shown]
Conventional physical therapy protocol

The therapists will have free choice to use feedbacks, and their instructions will be more related to the execution of the exercise than to the stimulus of self-knowledge of the patient. In this way, the warm-ups will have active joint mobilization exercises, increasing the speed of movement progressively according to the therapist’s command to the group. In the “back to calm” stage, breathing exercises will be performed, starting from diaphragmatic exercises to sustained inspiration and inspiration in times with the association of the upper limbs.

The training will follow the same EMPOWER-PD base structure (mixed, varied, and in blocks), featuring walking in solo, sit-and-lift, and pivot training with specific progressions for each stage of the circuit and increasing the level of difficulty of the complete task by increasing the speed from the therapist’s command. All the participants recruited and enrolled to the CPh will be training at the same time as well as in the Empower-PD group. However, we will control the exercise intensity (55 to 85% of HR_max_, as described previously). The therapy will be in group but without doubles or trios. The materials used in this protocol are the same as the EMPOWER-PD with the addition of the timer to control the execution speed of the circuit in some stages of the CPh protocol. The description of the exercises and their progressions during each week are explained in Table 2.

**Table 2 Tab2:** Conventional physical therapy. 8-week physical therapy protocol, twice a week

Weeks/goals	Objective	Exercises	Instructions	Progression
First–second	Increase speed of execution from a comfortable speed to a fast speed.	From sitting, get up and walk in an 8-m track, make the turn to the “U” (1 m), and walk diagonally to sit on the next chair.	Get up from the chair and walk to the “U,” go around it and sit on the next chair. Start by performing at comfortable speed, with each command increasing speed (“a little faster”/“fast”/“as fast as you can without running”).	The “U” will decrease (1 m–80 cm pivot), and the height of the chair (50 cm–45 cm–40 cm). Every three repetitions of the circuit will be given the command to increase the speed.

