#### Outcomes

##### Primary outcomes

Adherence will be assessed through retention and attendance rates. The retention rate will be analyzed by the percentage of participants completing all sessions of the intervention (16 in total) as well as the percentage of participants present in each step of study until the last evaluation at the follow-up period. Attendance rate will be analyzed by the mean of presences of the participants divided by the number of sessions offered during the 8-week intervention, multiplied by 100. The recruitment rate will be expressed by percentage and analyzed by the number of eligible individuals recruited per month. We will consider a recruitment and retained rate of > 80% as feasible to conduct a future randomized control trial. Safety will be reported by the number of adverse events. Adverse events were defined as exercise intolerance, injuries, or falls during the intervention [39], considering < 5% of occurrence of adverse as acceptable to conduct a future randomized control trial. The acceptability of the protocol by the participants will be better elucidated by the qualitative analysis in a general way (Fig. 4).

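### Only EMPOWER-PD has a scheduled talk after each session, so the comparison of adverse events between arms is open to unequal ascertainment of self-reported events

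*Protocol article*

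**What the plan says.** All places are in the protocol article.

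- **Primary outcomes.** Safety is reported as the number of adverse events: "Adverse events were defined as exercise intolerance, injuries, or falls during the intervention". An occurrence below 5% is taken as acceptable for a future trial. Neither the denominator nor whether the limit applies to each arm is stated.
- **Background, hypotheses.** "We hypothesize that the EMPOWER-PD will lead to higher adherence and safety when compared with conventional physical therapy".
- **Empower-PD.** Besides feedback on individual tasks, "at the end of each session, a talk wheel is held about their perceptions of the session and the repercussion under their daily routine".
- **Section on conventional physical therapy (CPh).** "In the “back to calm” stage, breathing exercises will be performed, starting from diaphragmatic exercises to sustained inspiration". On feedback: "The therapists will have free choice to use feedbacks, and their instructions will be more related to the execution of the exercise". No talk at the end of the session is described.
- **Interventions groups.** There are 16 sessions. Both arms have oximetry every 5 minutes and a modified Borg effort rating, with two physical educators per group. "Before and after each session, blood pressure will be measured".
- **Table 1, seventh and eighth weeks (EMPOWER-PD).** "the therapist will be co-adjuvant in therapy, always stimulating the confidence and tranquility of the group and appearing in a few moments". The Empower-PD section adds that these sessions remain supervised.

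**The concern.** A comparison of adverse-event counts is fair only if an event of a given kind has about the same chance of coming to light in each arm. Here the arms differ by design in how often participants are invited to say how the session felt and how it affected daily life. Overt falls and injuries in session can be seen by staff in either arm. Soreness, a minor strain, intolerance felt later or a fall at home come to light mainly when a participant mentions them, and only EMPOWER-PD has a regular occasion for that.

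The difference in counts then mixes true risk with opportunity to disclose. At stake are the reading of the safety hypothesis and the safety information carried into the definitive trial, from a study so small that one or two events matter.

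**Working it through.** The article gives no figure to reproduce. The check sets the arm descriptions side by side and then asks what size can be supported.

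**1. Ways an event can come to light, as written**

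| Route | EMPOWER-PD | CPh |
|---|---|---|
| Staff present in session | yes; therapist less active in weeks 7–8 | yes, therapist-directed throughout |
| Borg effort rating and oximetry | yes | yes |
| Blood pressure before and after the session | yes | yes (stated for the sessions in general) |
| Scheduled talk after the session | every session (16 of 16) | none described |

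Only the last row differs throughout. The first differs in weeks 7–8: 2 weeks × 2 sessions = 4 of 16 sessions (25%).

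**2. Which events are exposed**

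Falls and overt injuries in session are visible in both arms. Exertion is asked about in both arms through the Borg rating. What remains is minor injury, delayed intolerance and, if the definition covers the 8-week period and not only the sessions, falls between sessions.

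**3. Possible size (assumed inputs)**

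Let x be the share of events that surface only when participants are asked. Assume that EMPOWER-PD captures all of these and CPh none. At equal true risk, the recorded ratio EMPOWER-PD : CPh is 1/(1 − x):

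- x = 0.10: 1/0.90 = 1.11
- x = 0.50: 1/0.50 = 2.0

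Now let y be the share of events missed in EMPOWER-PD during the four sessions in which the therapist steps back, with events spread evenly and the talk recovering none of them. The ratio is (1 − 0.25y)/(1 − x). At the extreme y = 1:

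- x = 0.10: 0.75/0.90 = 0.83
- x = 0.50: 0.75/0.50 = 1.5

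The extreme is not realistic, because the sessions stay supervised. It does show that the net direction depends on two quantities that the article does not give.

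**4. Sensitivity of the 5% limit**

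With 12 per arm (Sample size section):

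- Per participant, one arm: 1/12 = 8.3%, above the limit.
- Per participant, both arms: 1/24 = 4.2%, below it.
- Per participant-session, one arm: 12 × 16 = 192 at full attendance, and 5% of 192 = 9.6 events.

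On the per-participant, per-arm reading, the chance of recording at least one affected participant is 1 − (1 − p·d)^12, with p the assumed true risk and d the assumed share detected:

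| p | d = 1.0 | d = 0.8 | d = 0.6 |
|---|---|---|---|
| 0.05 | 0.46 | 0.39 | 0.31 |
| 0.10 | 0.72 | 0.63 | 0.52 |
| 0.20 | 0.93 | 0.88 | 0.78 |

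On the per-session reading with x = 0.20, 10 true events per arm give 10/192 = 5.2% against 8/192 = 4.2%, on opposite sides of the limit. That split is narrow. At 9 true events both arms are below it (9/192 = 4.7% in EMPOWER-PD). At 12, CPh is expected to record 12 × 0.8 = 9.6, or 5.0%, so neither arm is below 5%. Only 10 or 11 true events separate the arms.

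**The case against.** The case against has several parts.

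- **The talk is part of the intervention and is not named as a source of adverse events.** True. Unequal ascertainment does not need the label, though: staff who hear of an injury in the talk then know of it.
- **A condensed article may leave adverse-event recording to the full protocol.** Also true, so the absence of a described form is not the point. The point is a difference between arms that the article does state. A shared form would not by itself equalise the occasions to disclose; a shared question would largely do so.
- **CPh participants are asked about exertion too.** This stands. A reader might infer that CPh has no route for reporting at all, 0 of 16 sessions against 16 of 16. That ignores the Borg rating and the supervision in both arms. The contrast holds only for the scheduled talk.
- **The planned comparison is thin.** Only aims (ii) and (iii) are worded as comparisons, and the Data management and analysis section reports safety as numbers. This lowers the stakes, but the stated hypothesis sets the arms against each other on safety.
- **The direction is conservative or unknown.** The talk alone would add events to EMPOWER-PD, against the trial's hypothesis, while the therapist's reduced role in weeks 7–8 could hide some. This stands.
- **The 5% rule is not stated per arm.** This stands. A reader might infer that CPh would pass a rule that EMPOWER-PD fails; the article sets no such arm-by-arm decision.

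**Conclusion.** The comparison of adverse events between arms is open to differential ascertainment of self-reported events. It would go too far to say that the comparison is biased, or that EMPOWER-PD will look less safe: the article does not show how many events surface only on asking, or how much the weeks 7–8 arrangement offsets the talk.

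The ratios of 1.11 to 2.0 illustrate an assumed 10% to 50% share, with full capture in one arm and none of that share in the other; they are not estimates. The exposure is confined to minor injury, delayed intolerance and, on the 8-week reading of the definition, falls between sessions. It still merits action because the counts will be small and the remedy uses contacts that already exist.

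**What to change.** At the blood-pressure measurements already taken before and after each session, ask every participant in both arms the same scripted question about falls, injuries and exercise intolerance during and since the last session. Record the answer on one form, with the source of each event: staff-observed, scripted question, or talk only.

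- **Contrast between arms:** use staff-observed and scripted-question events, and report talk-only events separately beside it.
- **The 5% safety rule:** count all known events, including those first disclosed in the talk. Leaving them out would discard known harms from the decision on a future trial.

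The cost is one question and a one-line form, and the intervention is unchanged. Somewhat more adverse events will be recorded overall. Some imbalance may remain: the article does not give the order of the talk and the post-session measurement, so the talk could prompt answers to the scripted question.

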##### Conventional physical therapy (CPh)

The sessions are given by two physiotherapists and unlike EMPOWER-PD, a conventional physical therapy will not address motivational factors available in the preferences of the individual and during all sessions. The physiotherapist will be the main responsible for assembling, controlling, and directing the interventions in relation to each proposed exercise, their durations, intensities, and frequency for all the 8 weeks (Fig. 3).

**Fig. 3 Fig3:**
[figure not shown]
Conventional physical therapy protocol

The therapists will have free choice to use feedbacks, and their instructions will be more related to the execution of the exercise than to the stimulus of self-knowledge of the patient. In this way, the warm-ups will have active joint mobilization exercises, increasing the speed of movement progressively according to the therapist’s command to the group. In the “back to calm” stage, breathing exercises will be performed, starting from diaphragmatic exercises to sustained inspiration and inspiration in times with the association of the upper limbs.

The training will follow the same EMPOWER-PD base structure (mixed, varied, and in blocks), featuring walking in solo, sit-and-lift, and pivot training with specific progressions for each stage of the circuit and increasing the level of difficulty of the complete task by increasing the speed from the therapist’s command. All the participants recruited and enrolled to the CPh will be training at the same time as well as in the Empower-PD group. However, we will control the exercise intensity (55 to 85% of HR_max_, as described previously). The therapy will be in group but without doubles or trios. The materials used in this protocol are the same as the EMPOWER-PD with the addition of the timer to control the execution speed of the circuit in some stages of the CPh protocol. The description of the exercises and their progressions during each week are explained in Table 2.

**Table 2 Tab2:** Conventional physical therapy. 8-week physical therapy protocol, twice a week

Weeks/goals	Objective	Exercises	Instructions	Progression
First–second	Increase speed of execution from a comfortable speed to a fast speed.	From sitting, get up and walk in an 8-m track, make the turn to the “U” (1 m), and walk diagonally to sit on the next chair.	Get up from the chair and walk to the “U,” go around it and sit on the next chair. Start by performing at comfortable speed, with each command increasing speed (“a little faster”/“fast”/“as fast as you can without running”).	The “U” will decrease (1 m–80 cm pivot), and the height of the chair (50 cm–45 cm–40 cm). Every three repetitions of the circuit will be given the command to increase the speed.
Third–fourth	Develop the ability to adapt gait and sit and lift to different sensory contexts.	From sitting, get up and walk 8 m (passing and skirting obstacles, through narrow spaces of 60 cm, holding objects and etc.) to the “U” (80 cm), skirt and sit on the next chair.	Get up, walk, go through the challenges encountered along the circuit until you reach the “U,” go around it, and return to sit on the next chair.	The “U” will decrease (80 cm–60 cm pivot) and the height of the chair (45 cm–40 cm bench). Obstacles will grow taller and narrower; the spaces will rise to 50 cm, and they will exchange objects between them during the gait.
Fifth–sixth	Develop the ability to adapt gait and sit and lift to different sensory contexts under conflicting situations of double task.	From sitting, get up and walk 8 m under the same challenges of the previous week, but under more conflicting stimuli (talk during the task, different speeds, stop abruptly, traffic signal).	Get up, walk, go through the challenges encountered along the circuit until you reach the “U,” go around it, and sit on the next chair. I will post different conflicting situations in the course of the exercise.	Pivot at all ends and the height of the chair will continue from 45 cm–40 cm bench. The progression will be made in the following order: noise in the room, talk during the task, different speeds, stop abruptly, and traffic signal.
Seventh–eighth	Increase running speed of the walking circuit and sit and lift in different sensory contexts and conflicting situations (≤ 3 s from first to last lap).	From sitting, get up and walk by 8 m under the same challenges of the previous week, but under more conflicting stimuli (talk during the task, different speeds, stop abruptly, traffic signal).	Get up, walk, go through the challenges of the circuit until you reach the “U,” go around it, and sit on the next chair. I will post different conflicting situations during the exercise and every three laps I will ask you to increase the speed (“a little faster”/“fast”/“as fast as you can without running”).	The progression will continue the same as the previous week, but the increase speed command will be added every three repetitions of the circuit.

Legend: *m* meters; *cm* centimeter

